Social motives are also associated with specific hormones [33,34]. Being inferior, for example, in a contest situation, has been associated with a decrease in testosterone in men with strong power motives [35]. For high power–motivated women, motive frustration leads to a decrease in estradiol [35]. Arousal of the affiliation motive is accompanied by an increase in progesterone for both sexes [33,36,37]. Furthermore, social motives in relationship with stress have been associated with various parameters of health, including blood pressure and the immune system [20], medication use and somatic symptoms [38], or job burnout and physical symptoms [39]. In summary, previous research has confirmed that affiliation and power motives lead to differential emotional, behavioral, and physiological responses to social cues. 

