#### Hypothesis 3: Motive-Specific Arousal Hypothesis 

Participants with strong affiliation and power motives respond to social support with arousal of self-reported motive-specific affect (ie, affiliation: joy and feeling socially related; power: feeling weak and inferior) and with an increase in motive-specific reproductive hormone responses* *(affiliation: progesterone; power: estradiol and testosterone).

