#### Hypothesis 4: Sex Difference Hypothesis

Women and men are hypothesized to differ in their social motives, with higher affiliation and lower power motives in women than in men. Women and men will specifically respond to social support with relative increases in estradiol and progesterone in women and testosterone in men.

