### Statistical Analysis

Statistical analysis will be performed using IBM SPSS Statistics, Version 28 (IBM Corp) for Windows (statistical analysis and graphs). We will perform an analysis of variance with repeated measures to determine if the TSST procedure results in significant increases in psychological and biological variables for all participants. We will calculate multiple linear regressions to examine interaction effects. In these regressions, we will first include the control variables, then the condition as a dummy variable, and finally the individual predictors and their interaction terms. To account for repeated measurements of the collected hormones, the area under the curve with respect to increase will be calculated and used as a dependent variable [71]. As an additional effort to ensure that participants with a delayed significant increase in their hormones will not be excluded, an adjusted increase value will be calculated, regardless of the time of measurement. This value will be obtained by subtracting the baseline value from the peak value. Multiple regressions will be calculated again with these adjusted values. Nonbiological dependent variables, such as those obtained from the psychological test battery, will be added as means. Only data from individuals who have fully completed the TSST protocol will be included in the final analyses. Missing data will be added by multiple imputation.

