## Discussion

The aim of this study is to investigate whether social motives and participants’ sex moderate the effect of social support in stressful situations. We expect that participants with a strong affiliation motive will benefit from social support in terms of reduced psychobiological stress responses when being critically evaluated by others. For those participants, social support is supposed to serve as a stress buffer. In contrast, social support is expected to act as a stress amplifier in participants with a high-power motive, resulting in higher psychobiological stress responses.

To elucidate the influence of implicit social motives on affect in specific situations, we will record participants’ motive-specific affect. We postulate that participants with a high affiliation motive, will respond to social support with affiliation and an increase in progesterone. Participants with a high power motive will show feelings of inferiority and a decrease in testosterone or estradiol.

To explore the influence of implicit motives without bias, we also consider sex as a variable in our study. It is hypothesized that males exhibit a higher power motive and females exhibit a higher affiliation motive. This is expected to be reflected in motive-specific hormones.

Some studies have shown that social support has positive effects [72], while others have reported no, small, or adverse effects of social support [73,74]. With the introduction of implicit motives as moderator variables, as well as taking sex into account, we strive to explain why people react differently in same situations. Through this person-situation approach, we enable a more differentiated view on the effect of social support in stress situations. In summary, with this sophisticated view, we aim to provide a foundation that interventions could be designed in an individualized way and therefore only produce positive effects and no adverse effects.

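### Hypothesis 3 and the Discussion predict opposite signs for testosterone and estradiol in power-motivated participants who receive support

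*Protocol article*

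**What the plan says.** Four parts of the protocol article give a direction for testosterone and estradiol.

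- **Implicit Motives (background).** Being inferior "has been associated with a decrease in testosterone in men with strong power motives". For power-motivated women, "motive frustration leads to a decrease in estradiol".
- **Hypothesis 3.** Strong power motive plus support is expected to produce feelings of weakness and inferiority, together "with an increase in motive-specific reproductive hormone responses", with estradiol and testosterone named for power.
- **Hypothesis 4.** Under support, "relative increases in estradiol and progesterone in women and testosterone in men" are expected. This is a statement by sex; motive is not mentioned.
- **Discussion.** "Participants with a high power motive will show feelings of inferiority and a decrease in testosterone or estradiol".

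For the analysis, the Statistical Analysis section plans linear regressions with interaction terms. For the repeated hormone measurements, "the area under the curve with respect to increase will be calculated and used as a dependent variable". As an extra step, "an adjusted increase value will be calculated, regardless of the time of measurement", defined as follows: "This value will be obtained by subtracting the baseline value from the peak value". The regressions are then repeated on that second value.

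**The concern.** Hypothesis 3 is one of the five numbered hypotheses and is listed apart from the exploratory one. It predicts a rise in two hormones. The Discussion predicts a fall in the same hormones, for the same motive and the same exposure. Hypothesis 3 also pairs its rise with feelings of inferiority, which the background links to a fall. Nothing in the article reconciles these statements.

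A directional hypothesis earns its evidential weight by ruling out one sign. With both signs in print, neither is ruled out for these hormones. The timing adds to this: registration was retrospective, the start of the experiment is given as June 2021, and the protocol version is dated May 22, 2022. The document therefore needs to show one fixed prediction.

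**Working it through.** The article gives no figure to reproduce here. The check sets the sections side by side and then applies the two planned outcome definitions.

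**1. Direction by section**

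| Section | Condition | Testosterone | Estradiol |
|---|---|---|---|
| Implicit Motives | power motive, inferiority or frustration | decrease (men) | decrease (women) |
| Hypothesis 3 | power motive, support | increase | increase |
| Hypothesis 4 | support, by sex only | relative increase (men) | relative increase (women) |
| Discussion | power motive, support | decrease | decrease |

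Hypothesis 3 joins the two hormones with *and*; the Discussion joins them with *or*. Progesterone with the affiliation motive is an increase in both places, and the power-motive affect (inferiority) also agrees.

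**2. Consequence for the test**

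Let b be the support × power-motive coefficient. Hypothesis 3 implies b > 0 and the Discussion implies b < 0. Assume a two-sided 5% level (the article states none). With no effect, 2.5% of tests are significant on each side. If one sign counts as confirmation, the false-confirmation rate is 2.5%; if either does, it is 2.5% + 2.5% = 5%.

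**3. What the two outcomes can show**

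Reproductive hormones are sampled at −11, 0, +20 and +65 min, a span of 76 min. AUCi is the trapezoid area minus baseline × 76.

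- Illustrative profile 100, 95, 90, 85: 97.5×11 + 92.5×20 + 87.5×45 = 6860, and 6860 − 7600 = **−740**. Peak minus baseline is 0 if the baseline sample may be the peak, and −5 if only later samples count.
- Illustrative profile 100, 102, 80, 70: 101×11 + 91×20 + 75×45 = 6306, and 6306 − 7600 = **−1294**. Peak minus baseline is **+2** under either definition.

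**4. Upward bias of peak minus baseline**

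Assume independent within-person noise of 1 SD and a peak taken over the three later samples. The expected maximum of three standard normal values is about 0.85. With a true shift of −d at every later sample, the mean is 0.85 − d:

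- d = 0: +0.85 SD
- d = 0.5: +0.35 SD
- d = 1: about −0.15 SD

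The mean of AUCi with no true change is about 0.

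**5. Effect on the interaction coefficient**

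Simulation assumptions: baseline 100, within-person SD 10, N = 154 split equally, standard normal motive score, and a true interaction of −5 per SD of motive (half of it at 0 min, all of it at +20 and +65 min). There were 1,500 runs.

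| Outcome | Significant, negative | Significant, positive |
|---|---|---|
| AUCi | 66% | 0% |
| Peak minus baseline, baseline may be the peak | 48% | 0% |
| Peak minus baseline, later samples only | 54% | 0% |

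The article gives 154 participants under Sample Size and Recruitment and 308 in the Abstract. At N = 308 the negative column reads 91%, 77% and 82%; the positive column stays at 0%.

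**The case against.** **It is only wording in part of one hypothesis.** The scope is indeed narrow: two hormones, one motive, one of five hypotheses. No sample size or model changes. But the sign is the content of a directional prediction, and the article prints both.

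**Sidedness can be left to an analysis plan.** This is fair, and the missing direction in the Statistical Analysis section would not be a finding by itself. It matters because the article states two opposite predictions and nothing in it chooses between them.

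**Hypothesis 4 also predicts increases.** It does, by sex and in relative terms. A sex effect and a power-motive effect of opposite sign could coexist, so Hypothesis 4 does not settle the matter. It is, however, a reason not to assume that the Discussion's direction is the intended one.

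Three stronger readings are tempting but not supported.

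- *That the planned hormone outcome cannot show a decrease.* AUCi is named first, is signed and can be negative. Peak minus baseline is an additional analysis. It has a strict floor at zero only if the baseline sample may be the peak, which the article leaves open. With later samples only, its mean turns negative at a 1 SD fall.
- *That the peak-based regression would have the wrong sign.* Taking a maximum raises the mean of the outcome. The hypothesis is tested through a between-person coefficient, which is attenuated; no significant result in the wrong direction appeared in the simulation. Nor is the peak outcome the reason that either sign could be claimed as predicted; that comes from the text alone.
- *That the plan pools the sexes and loses power.* Study Design lists sex as a between-subject factor, and the article does not exclude a sex interaction from the hormone models.

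**Conclusion.** The contradiction stands. Hypothesis 3 and the Discussion give opposite signs for testosterone and estradiol under a strong power motive with support. The background agrees with the Discussion, and the article does not reconcile them. Either sign of a significant interaction could be reported as predicted, which takes false confirmation from 2.5% to 5% per test at an assumed two-sided 5% level. The affiliation–progesterone prediction and the affect predictions keep a fixed direction.

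Peak minus baseline is a secondary matter. If the chosen direction is a decrease, it is a poor measure: biased upward by about 0.85 SD under independent noise, with detection of 48–54% against 66% for AUCi in the simulated setting at N = 154. Those sizes depend on the assumed noise, effect and time course. The ordering, with AUCi the more sensitive to the simulated fall, was the same at N = 308.

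**What to change.** 1. Reconcile the background on implicit motives, Hypothesis 3, Hypothesis 4 and the Discussion to one direction per hormone for the power motive, and per sex if the rationale is sex-specific. The authors must choose the direction.
2. State it as the expected sign of the support × power-motive coefficient. Say whether the prediction needs both hormones or either one. Record it, with a date, before the hormone data are analysed.
3. Name the signed AUCi as the outcome that tests it.
4. If a decrease is predicted, label peak minus baseline as supplementary for testosterone and estradiol, and state whether the baseline sample may count as the peak. This point gives no reason to change its use for progesterone.

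The cost is rewording and a less prominent secondary outcome for two hormones. No new data or participants are needed.

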#### Hypothesis 4: Sex Difference Hypothesis

Women and men are hypothesized to differ in their social motives, with higher affiliation and lower power motives in women than in men. Women and men will specifically respond to social support with relative increases in estradiol and progesterone in women and testosterone in men.

#### Hypothesis 5: Speech Performance Hypothesis

Participants who receive social support show better presentation performance in TSST interviews than participants in the no social support group. This relationship is moderated by social motives. Participants in the social support group perform better when the affiliation motive is high and perform worse when the power motive is high.

#### Exploratory Hypothesis: GRSC

On an exploratory level, we plan to investigate the association of self-reported GRSC with social motives and their moderating role on whether individuals of either sex benefit from social support.

## Methods

### Study Registration

This study was retrospectively registered in the German Clinical Trials Register (DKRS) on March 09, 2022, under the following number: DRKS00028503. The trial was not prospectively registered because COVID-19 restrictions led to uncertainty about whether, when, and under what circumstances (eg, wearing a FFP2 mask) data collection could take place.

### Study Design

The study is based on a mixed within- and between-subject design. The within-subject factors are participants’ stress responses (self-reports and biological markers) across the steps of the TSST procedure (Figure 1). The between-subject factors are experimental groups (social support vs no social support), social motives, and participants’ sex. GRSC and other control variables will be assessed as controls and entered as covariates into the analysis models. Allocation will be based on a 1:1 ratio. There will be no cross-over into the experimental group.

The study will be conducted in the laboratory of sports psychology of the Department of Sport Science at the University of Konstanz, Germany. The analyses of hormones and α-amylase will be performed in the biochemical laboratory of the Institute for Medical Psychology in Heidelberg, Germany.

### Ethics Approval

The study was approved by the Institutional Review Board of the University of Konstanz on December 18, 2018 (35/2018). Further, the participants will receive a study information sheet and give their informed consent in the screening online survey (Multimedia Appendix 1) before the laboratory session. If they fulfill the inclusion criteria, they will be invited to the laboratory session. Here, the participants will again read the study information sheet and sign the informed consent (Multimedia Appendix 2). Participants can discontinue the study at any time without giving any reason. They will still receive their payment.

To ensure confidentiality**,** personal data (email addresses) of potential and enrolled participants will be collected by the principal investigator and stored password-protected on the local university server. The information will not be shared.

### Blinding

Participants and all experimenters involved in data collection and processing (eg, motive coders), with the only exception of social support providers, will be blinded to the intervention after assignment.

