#### Preparation Phase of the TSST-G Without Social Support

For the preparation phase, each participant sits in a separate room. Here, they receive written instructions for the upcoming interview (Multimedia Appendix 5). After they have had 10 minutes of preparation time for this task, they give a saliva sample (T1, 0 min) and complete the psychological questionnaire again. Subsequently, the participants are individually led to their places in front of the panel.

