#### Preparation Phase of the TSST-G With Social Support

The preparation phase is identical to the described scenario for the participants without social support, with the exception that the experimenter introduces a female associate as a student assistant who can assist the participants if needed. The female associate provides passive social support for the first 5 minutes, ostensibly working on the computer. In the second 5 minutes of the preparation phase, the associate gives active social support and also notes the reactions of the participants (Multimedia Appendix 6). At the end of the 10-minute preparation period, the associate asks the participants for a saliva sample (T1, 0 min) and tells the participants to complete the psychological questionnaire again. Then, rooms are changed. All other instructions are the same as in the group without social support.

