#### TSST-G

##### Psychosocial Stress Induction

Our procedure is based on the TSST-G developed by Von Dawans et al [49]. Each participant is required to present his or her interview individually in front of the panel for 3 minutes at a time. During this time, the participant is interrupted in a standardized manner by the panel (Multimedia Appendix 7). After that, they give a saliva sample (T2, +12 min) and complete the psychological questionnaire. Subsequently, each participant has to perform the arithmetic task 3 times for 30 seconds. When this task is finished, they give another saliva sample (T3, +20 min). During this whole procedure, the participants are recorded with a microphone and a camera. The experimenter then leads the participants individually from the TSST-G test room to the respective preparation rooms. Here, they again fill in the psychological questionnaire.

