##### Rest Phase

During the rest period, 3 additional saliva samples are collected (T4, +30 min; T5, +45 min; T6, +65 min). Participants who have received social support will complete a social support scale at T6 (+65 min) (Multimedia Appendix 8).

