### Data Management

The questionnaire data will be downloaded from Limesurvey and stored on the university server. The psychological questionnaire from T2, which will be collected by paper and pencil format, as well as heart rate and heart rate variability will be stored in an Excel table by the study experimenter directly after the study. The video file will also be saved directly after the experiment, on a laptop of the sport psychology laboratory and a back-up server. The saliva samples will be sent to the biochemical laboratory of the Institute for Medical Psychology in Heidelberg, Germany. To guarantee the accuracy of the analyses, 10% of the cortisol samples and 20% of the samples for reproductive hormones will be double assessed. The signed consent forms of the participants will be collected in the sport psychology laboratory in Constance. Only the experimenter will have access to the data, which will be stored for 10 years on a server of the University.

The participants will generate their own code that allows to merge the data of the web surveys with the data obtained in the laboratory.

Saliva samples will be stored in the biochemical laboratory at Heidelberg University Hospital for at least 2 years after completion of the study and will then be discarded.

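### The blinding statement exempts only support providers, but the experimenter who introduces the associate also knows the arm; separately, T1 is requested differently in the two arms

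*Protocol article*

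**What the plan says.** The Blinding section covers participants and every experimenter who takes part in collecting or processing data. It makes one exemption: "with the only exception of social support providers, will be blinded to the intervention after assignment". Motive coders are its only named example.

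The procedure sections describe the session as follows.

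- **Support arm, preparation phase:** "the experimenter introduces a female associate as a student assistant who can assist the participants if needed". In the second five minutes "the associate gives active social support and also notes the reactions of the participants". At minute 10 "the associate asks the participants for a saliva sample (T1, 0 min) and tells the participants to complete the psychological questionnaire again".
- **Control arm, preparation phase:** participants sit in separate rooms, and after the same ten minutes "they give a saliva sample (T1, 0 min) and complete the psychological questionnaire again". No requester is named.
- **After the arithmetic task (Psychosocial Stress Induction):** "The experimenter then leads the participants individually from the TSST-G test room to the respective preparation rooms". The next questionnaire is filled in there.
- **Data Management:** the paper T2 questionnaire, "as well as heart rate and heart rate variability will be stored in an Excel table by the study experimenter directly after the study".
- **Rest Phase:** "Participants who have received social support will complete a social support scale at T6".

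The Test Battery section gives seven questionnaire occasions. The Statistical Analysis section says that non-biological outcomes enter the regressions as means.

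**The concern.** There are two separate problems.

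The first is a contradiction. The plan claims a blinding property for all experimenters but one class, and its own procedure shows the arm to an experimenter outside that class. If the sentence is carried into the results paper, readers will credit the trial with blinded data collection that it did not have in full.

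The second is unequal assessment. T1 is the first self-report after support and the last before the panel. In one arm the person who has just been supportive asks for it; in the other arm no such person exists. The items are subjective (well-being, perceived stress, feeling socially related). A wish to please the associate could therefore be read as an effect of support on well-being or motive-specific affect.

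**Working it through.** **Step 1: is the blinding statement consistent with the procedure?** The plan gives no figure to reproduce, so the passages are set side by side.

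| Question | Where stated | Answer |
|---|---|---|
| Who is exempt from blinding? | Blinding | Support providers only |
| Who introduces the associate? | Preparation Phase With Social Support | The experimenter |
| Is that experimenter a support provider? | Same section | No; the associate is |
| Does the experimenter role have later contact? | Psychosocial Stress Induction | Yes, leads participants back before the next questionnaire |
| Does the experimenter role process data? | Data Management | Yes, stores the T2 questionnaire and heart-rate data |

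Whoever introduces the associate sees the arm. One such experimenter is enough to make the statement untrue, even if several people share the experimenter tasks.

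**Step 2: who requests T1?** The instrument, the timing and the saliva sample are the same in both arms. The requester is the associate in the support arm and is unnamed in the control arm, where there is no associate. The support-arm section says that all other instructions match, which leaves this difference in place.

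**Step 3: what could a difference at T1 do to the analysis?** Let *b* be the shift in a T1 self-report caused only by who asks for it, present in the support arm only. The documents give no value for *b*.

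- Contrast at T1 alone: the arm difference moves by *b*.
- Mean over all seven occasions: it moves by *b*/7, about 0.14*b*. The plan does not say which occasions form the mean, so seven is an assumption.

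For illustration, assume *b* = 0.2 to 0.3 single-occasion SD. Then 0.2/7 = 0.03 and 0.3/7 = 0.04. If a mean of only three occasions including T1 were used, 0.2/3 = 0.07 and 0.3/3 = 0.10. All are in single-occasion SD units; the SD of a mean is generally different, so these are not standardised effects on the analysed outcome.

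**Step 4: main effect or interaction?** Write the planned regression for one motive, with C the condition dummy and M the motive score, as

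Y = β0 + β1·C + β2·M + β3·C·M.

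- If *b* is the same for everyone, the seven-occasion mean gains (*b*/7)·C. Then β1 becomes β1 + *b*/7 and β3 is unchanged.
- If *b* = *b*0 + *b*1·M, the mean gains (*b*0/7)·C + (*b*1/7)·C·M. Then β3 becomes β3 + *b*1/7.

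For the self-reports, Hypotheses 2 and 3 concern moderation of the response to support by motive, so β3 is the term of interest. It is biased only if the response to being asked by the associate varies with motive.

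**The case against.** The strongest reply is that little beyond a wording slip has been shown. Several parts of that reply stand.

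- **A reader might infer that no one is blinded.** The documents do not support this. The Picture Story Exercise is completed online before the session and saliva is assayed at an outside laboratory. Nothing contradicts blinding of the motive coders or that laboratory.
- **A reader might infer that one unblinded person runs the whole session.** The text does not establish it. The control-arm section says participants are led to the panel without saying by whom, and the Harms section speaks of experimenters in the plural. What is documented is that the experimenter role covers the introduction, the return to the rooms and the data storage.
- **A reader might infer that the T6 support scale reveals the arm to staff.** The plan does not say who hands it out or sees it, so this is only a possible cue.
- **A reader might take the associate's role at T1 as a second breach of the blinding statement.** It is not, because her knowledge of the arm is disclosed there. Nor does she administer the questionnaire: she asks for a self-completed form, and the text does not say she stays while it is answered. The point at T1 is unequal assessment. Detailed scripts are in appendices that are not shown.
- **A uniform politeness effect cancels from the interaction tests.** This is correct, as Step 4 shows. The Introduction does describe affiliation-motivated people as wanting warm, friendly relations, so a shift that rises with that motive is conceivable. That is an inference, not something the plan demonstrates.

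The reply does not remove the contradiction. The article states both the rule and the step that breaks it, so an unseen appendix cannot make both true.

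**Conclusion.** The point holds in a limited form. The blinding sentence is wrong about at least the experimenter who introduces the associate, and that role also handles participants and data afterwards. This follows from the text with no assumption. The T1 self-reports are requested differently by arm, which is also plain from the text.

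The consequence at T1 is uncertain and probably small for averaged outcomes. Under the assumed 0.2 to 0.3 SD it is 0.03 to 0.04 SD in a seven-occasion mean, while a contrast at T1 alone would carry all of it. A reader might conclude that the self-report findings are biased towards support being helpful. The documents do not show that: the size of *b* is unsourced, and the support-by-motive tests are affected only if *b* varies with motive. The correction is still worth making, because the blinding claim would otherwise be reported inaccurately and the difference at T1 is cheap to remove.

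**What to change.** 1. **Correct the Blinding section.** State that the associate and the session experimenter who introduces her know the condition. Claim blinding only for roles that do not see it, such as the motive coders and the saliva laboratory. Include the panel and the speech raters only if they are in fact kept unaware.
2. **Equalise T1 in the remaining sessions.** Have the experimenter, not the associate, request the T1 sample and questionnaire, with identical wording in both arms. The protocol version is dated May 2022 and collection runs to the end of 2022, so sessions remained when it was written.
3. **Add a sensitivity analysis.** Repeat the self-report analyses without T1. Keep T1 in the main analysis, since it is the only self-report taken directly after support and before the panel.

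The cost is a few sentences of text, a small change to the session script with existing staff, and one additional analysis. The downside is a small procedural difference between earlier and later sessions. The T1 change makes assessment equal across arms; it does not restore blinding of the experimenter, so the corrected statement is needed in any case.
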